**Socio-demographic**				
Education status	•			
Postcode	•			
Family history				
Sarcoma in relative <45 years	•			
Glioma or childhood adrenal cortical carcinoma	•			
Multiple cancers in family at a young age	•			
Jewish ancestry	•			
**Outcomes**				
Risk perception				
Breast cancer risk perception (absolute)	•	•	•	•
Breast cancer risk perception (comparative)	•	•	•	•
Breast cancer risk conviction	•	•	•	•
Recall of risk information		•	•	•
Psychological				
Anxiety [22]	•	•	•	•
Cancer-specific worry [21]	•	•	•	•
Quality of life [24]	•	•	•	•
Impact of cancer risk assessment [27]		•	•	•
Satisfaction with test		•		
Views on the risk information [33]		•		
Attitude towards risk management options		•	•	•
Lifestyle and behavioural				
Current behaviour (breast self-examination)	•	•	•	•
Intention to attend screening	•	•	•	•
Change in behaviour (weight, alcohol consumption, exercise)		•	•	•
Healthcare utilisation	•			•
Actions following risk assessment (moderate/high risk or those with additional risk factors)				
Consultation with GP (or intention if not done)		•	•	•
Uptake of risk reduction strategies (or intention if not done)				
Enhanced screening		•	•	•
Risk reducing medication		•	•	•
Surgery		•	•	•
Process evaluation				
Acceptability [26]	•		•	
Motivations and concerns	•			
Views on GP consultation (only for moderate/high risk or those with additional risk factors)		•		
**Moderators**				
Numeracy [28]	•			
Health literacy [29]	•			
Beliefs about breast cancer [30]	•			
Time orientation [31]	•			
Intolerance of uncertainty [32]	•			

Table 2 specifies all measures, instruments and data collection points (baseline and at 1, 3 and 6 months after receiving the risk assessment results). All outcomes will be measured by self-report and include risk perception, psychological impacts of the risk assessment, lifestyle and behaviour, and actions taken following the risk assessment. Risk perception will be assessed using questions about absolute and comparative risk, risk conviction and recall of risk. Psychological measures include cancer-related worry, anxiety and quality of life using the Lerman cancer worry scale [21], the short-form of the state scale of the Spielberger State Trait Anxiety Inventory (STAI) [22] and the EQ-5D-5L [23, 24] respectively. These have been chosen as the Lerman cancer worry scale and short-form STAI have been widely used in the literature and so will allow comparison with other studies, and the EQ-5D-5L is the recommended measure for use in economic analyses by NICE [25]. We will also collect data on: motivations and concerns regarding participation in the study using multiple choice questions and short open text boxes questions; the acceptability of the study using 5-point Likert scale questions [26]; the impact of cancer risk assessment using the MICRA scale [27]; satisfaction with the test using 5-point Likert scale; questions assessing the degree of satisfaction with the multifactorial cancer risk assessment; views on the risk information using 5-point Likert scale questions assessing the information in the CanRisk report; views on the GP consultation, including assessing the usefulness of the consultation and whether the appointment clarified understanding of breast cancer risk. Additionally, patients who agree to have their appointment recorded will receive an optional survey immediately after their GP consultation exploring their experience of the appointment. Attitudes towards risk management options (i.e., earlier or more frequent screening, medication and surgery) will also be measured via standardised scales and multiple-choice questions reviewed by patient and public partners. Lifestyle and behavioural data will be collected through multiple choice questions; these will include question about current behaviour regarding breast self-examination, intention to attend screening, change in behaviour (i.e., weight, alcohol consumption and exercise) and healthcare utilisation (i.e., number and type of contact) specifically focusing on breast health in the six months prior to baseline and six months after baseline. Data on actions following the risk assessment will only be collected for women found to be at increased risk and if they have attended the GP appointment. Actions measured will include multiple choice questions about the attendance at the GP appointment (or intention if not done) as part of the study and uptake (or intention if not done) of risk reduction strategies (i.e., earlier or more frequent screening, medication and surgery). We will also collect data on numeracy [28], health literacy [29], beliefs about breast cancer [30], time orientation [31], and intolerance of uncertainty [32]. These will be considered as moderators for the measures above that will help test interactions between variables in the study.

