## Study outcomes and measures

The study aims to generate data on the following outcomes:

Uptake of multifactorial breast cancer risk assessment, including the proportion of those invited who consent and the proportion of those invited who complete the breast cancer risk assessment, with or without the inclusion of the polygenic risk score.Distribution of breast cancer risk, including the proportion of women who consent who are at moderate or high risk on the initial CanRisk assessment in general practice (with or without the PGS) and those at moderate or high-risk following assessment in secondary/tertiary care.Proportion of women at moderate or high risk of breast cancer. The proportion of registered women aged 40–48 years at the start of the study at participating practices who are at moderate or high risk of breast cancer after assessment in secondary/tertiary care will be compared with the proportion of women aged 40–48 years at moderate or high risk of breast cancer after referral to secondary/tertiary care at non-participating practices across Cambridgeshire and Peterborough during the same time period, and also compared with the proportion of registered women aged 40–48 years at participating practices in the 12 months prior to the study.Uptake of risk-reducing interventions, including the proportion of those at moderate or high risk who attend for a GP appointment, are referred to secondary/tertiary care, and take up enhanced screening and/or preventative medication.Completeness of risk factor information collected through MyCanRisk, including the presence of information completed for non-family history risk factors (e.g., height, weight, alcohol, women’s health) and the number of family members included in the pedigree.Change in psychological and behaviour measures (Table 2) following multifactorial breast cancer risk assessment at one month, three months, and six months after receiving the risk estimate.Acceptability of the pathway of proactive multifactorial risk assessment within general practice to women and GPs, including response rates and completion of questionnaires and the willingness for practices to take part.Costs and workload associated with delivery of proactive multifactorial risk assessment.

**Table 2 pone.0336902.t002:** Assessments.

Construct	Baseline	1 month	3 months	6 months

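### The rule limiting post-assessment action items to women who attended the GP appointment contradicts the next sentence and Table 2, and needs to be reconciled with them.

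*Protocol article*

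**What the plan says.** The passages below are all in the protocol article.

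- **Study outcomes and measures, text under Table 2.** Data on actions following the assessment "will only be collected for women found to be at increased risk and if they have attended the GP appointment". The next sentence describes what is asked: "Actions measured will include multiple choice questions about the attendance at the GP appointment (or intention if not done) as part of the study", followed by uptake of risk-reduction strategies, again with intention as the alternative.
- **Table 2, action block.** It is headed "Actions following risk assessment (moderate/high risk or those with additional risk factors"). Its first item is "Consultation with GP (or intention if not done"), marked at 1, 3 and 6 months. Enhanced screening, risk-reducing medication and surgery follow at the same times. No attendance condition appears.
- **Study outcomes and measures, list of outcomes.** The uptake outcome includes "the proportion of those at moderate or high risk who attend for a GP appointment, are referred to secondary/tertiary care", and then uptake of enhanced screening or preventative medication. The denominator is all women at moderate or high risk.
- **Data source.** The text under Table 2 says "All outcomes will be measured by self-report". The Data collection section adds extraction from GP records for all consenting women, including coded uptake for those at moderate and high risk. It also adds aggregate referral data from the clinical genetics clinic.

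**The concern.** A woman who has attended cannot be in the not-done state. Under the restrictive sentence, the item on "attendance at the GP appointment (or intention if not done) as part of the study" would therefore reach only women for whom the answer is already known. The women for whom the intention wording was written would not be asked.

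The stake is the first step of the cascade that the study wants to measure. The Aims and objectives section says that uptake of risk-reducing interventions among women at moderate or high risk will inform the sample size of a future trial. A questionnaire that conditions on attendance cannot estimate attendance. It gives uptake only among women who passed that step, and it is silent on what the others intend.

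**Working it through.** **1. The statements side by side**

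| Place | Who is asked the action items | Can a non-attender answer? |
|---|---|---|
| Text under Table 2, restrictive sentence | Increased risk and attended | No |
| Text under Table 2, next sentence | Implied: attenders and non-attenders | Yes, by stating intention |
| Table 2, action block | Moderate/high risk or additional risk factors | Yes, at 1, 3 and 6 months |

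The first row cannot hold together with the other two.

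**2. Inputs for the size (Sample size section)**

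- Women at above-population risk: 17% of 1,000 = 170.
- Attendance at the GP and referral: 80%.
- Loss to follow-up: 40%.

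**3. The plan's own figure**

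The plan gives a precision of ±5.7% at 80%. The Wald half-width with n = 170 is 1.96 × √(0.8 × 0.2 / 170) = 0.060, or 6.0 points; a half-width of 5.7 needs n of about 189. The stated figure is not reproduced, but nothing below depends on it.

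**4. Women without action data under the restrictive sentence**

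- All at-risk women: 170 × (1 − 0.8) = 34, leaving 170 × 0.8 = 136 who answer.
- After loss to follow-up: 170 × 0.6 = 102 responders. Of these, 102 × 0.2 = 20.4 (about 20) are skipped and 102 × 0.8 = 81.6 (about 82) answer.

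The 80% describes women who attend and are referred. If it is a joint proportion, attendance alone is at least 80%, so 34 and 20 are upper limits for women who do not attend at all. The plan attaches no time to the 80%. Women who attend late would also be skipped at the earlier questionnaires, and the documents give no figure for them.

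**5. Self-reported attendance**

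Respondents who attended divided by respondents = 136/136 = 100%, whatever the true attendance.

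**6. Effect on uptake depends on the denominator**

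Assume, since the protocol does not say, that non-attenders take up nothing. Uptake among all at-risk women is then 0.8 × uptake among attenders:

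| Uptake among attenders (assumed) | Uptake among all at-risk women |
|---|---|
| 10% | 8% |
| 30% | 24% |
| 50% | 40% |

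Dividing by attenders overstates uptake by 1/0.8 = 1.25. Dividing by all women at moderate or high risk, as the outcome is defined, does not: with 30% among attenders, 136 × 0.30 = 40.8, and 40.8/170 = 24%.

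**7. After the condition is removed**

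The questionnaire denominator becomes 170 (half-width 6.0 points at 80%), or 102 after loss to follow-up: 1.96 × √(0.16/102) = 0.078, or 7.8 points.

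**The case against.** The strongest reply is that this is a drafting slip. Two of the three statements already describe the sensible rule, and the attendance condition fits naturally with the one-month items on views of the consultation. The article is condensed and the questionnaires are not shown, so the documents do not establish that non-attenders are in fact skipped. That stands, and it makes this a contradiction to resolve rather than a proven flaw in the data. It does not remove the need to resolve it, because intentions not asked at the time cannot be recovered later.

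The second reply is that other sources cover the ground, and it largely stands. Coded uptake is extracted for all consenting women at moderate or high risk. Practice staff contact women who have not booked or consulted, and they record reasons for not wishing to consult (Risk categorisation and returning risk assessment results). Interviews are planned with up to 20 women who decline or do not complete parts of the study (Qualitative interviews). A reader might infer that the uptake outcome cannot be estimated, or that barriers among non-attenders go unstudied; the documents support neither. A reader might also infer that uptake will be overstated by a quarter. That needs attenders as the denominator, and the outcome is defined over "the proportion of those at moderate or high risk who attend for a GP appointment" and the later steps.

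Two gaps remain. No other source is described as recording intentions. For women at near-population risk with additional family-history features, who are in Table 2's action block and are also advised to see their GP, the Data collection section does not list coded uptake.

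**Conclusion.** The point holds as an internal contradiction about who is asked the action items. Applied literally, the restrictive sentence fixes self-reported attendance at 100%, leaves non-attenders' intentions unrecorded, and limits self-reported uptake to attenders. The number affected is at most about 34 of 170 at-risk women, or about 20 of 102 after loss to follow-up. This rests on the plan's own 17%, 80% and 40%, and on reading the 80% as a lower limit for attendance by the end of follow-up.

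The uptake outcome survives through GP records. The only part without a direct substitute is stated intention among non-attenders, together with uptake among non-attending women at near-population risk with additional features. None of the three progression criteria in the Sample size section uses these items. The error is confined to one sentence, but it should be put right before the uptake data are analysed.

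**What to change.** 1. In the text under Table 2, delete the attendance condition for the action items, so that they go at 1, 3 and 6 months to all women at moderate or high risk or with additional risk factors, as Table 2 shows. Keep the condition only for the items on views of the GP consultation.
2. Confirm which branching was fielded. If non-attenders were skipped, correct it for the remaining questionnaires and report how many women were skipped at each time point.
3. Report the uptake outcome over all women at moderate or high risk, as it is defined. Report women at near-population risk with additional family-history features separately, because adding them to the denominator would change the outcome.

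The cost is one sentence, a check of one branching rule, and a few extra questionnaire items for at most about 34 women at moderate or high risk, plus any non-attenders at near-population risk with additional features, whose number the plan does not give. Only data collection and reporting change.

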
### Data collection

The data collection process is shown in Fig 2.

Participant baseline data is collected via an online questionnaire.

Participant level follow-up data is collected via participant questionnaires at 1, 3 and 6 months after receiving the results letter and from the GP electronic medical records 6 months after the last participant has received the results letter for all individuals who have consented to participate in the study. This includes coded entries relating to breast symptoms, breast cancer risk and, for those at moderate and high risk, uptake of risk-reducing interventions.

Practice-level aggregated data on the age, ethnicity and Index of Multiple Deprivation of all eligible women will be extracted at the end of the study from the GP electronic medical records. Practice-level and aggregated individual level data on the number of referrals of women potentially at above population-level risk for breast cancer and the outcomes of those referrals for all practices across Cambridgeshire and Peterborough for the period of the study will also be extracted from the electronic health records at the clinical genetics clinic at Cambridge University Hospitals NHS Foundation Trust. For the practices participating in this study, the same data will be extracted for the 12 months prior to the study. Data on the number of women registered at each practice will be extracted from publicly available National General Practice profiles.

A mixed-methods process evaluation is being conducted alongside collection of outcome data to explore how proactive breast cancer risk assessment is delivered and perceived at practice and patient levels. The main four questions guiding this element of the study will focus on: 1) whether this feasibility study did what it was set out to do; 2) whether the different elements in the study design worked and why; 3) what the different stakeholders thought about CanRisk and how it was implemented in general practice: and 4) whether implementing CanRisk in general practice is acceptable. Data is collected from women, GPs conducting breast cancer risk consultations, and practice managers and/or research leads from the different research sites. Three sources of data contribute to this process evaluation.

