### Processes and interventions

#### Practice recruitment.

GP practice recruitment was supported by the Clinical Research Network (CRN) Eastern. They approached practices across Cambridgeshire and Peterborough that refer patients at increased risk of developing breast cancer to the clinical genetics service at the Cambridge University Hospital NHS Foundation Trust. Practices were recruited from different areas to maximise participant sociodemographic and ethnic diversity. Practices that agree to take part signed a practice agreement form. Reasons for practices declining to take part in the study were collected where possible.

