#### Risk categorisation and returning risk assessment results.

Based on the CanRisk breast cancer risk estimate and current NICE guidelines [7], participants are categorised into one of three risk groups: near population level risk, near population level risk but with additional features in the family history (i.e., sarcoma in relative < 45 years; glioma or childhood adrenal cortical carcinomas; complicated patterns of multiple cancers at a young age; Jewish ancestry), and moderate or high risk.

Women with an estimated breast cancer risk in the near population level risk group and without any additional risk factors based on their family history (see Table 1) receive a letter from the study team informing them that they are at near population level risk for breast cancer along with a breast awareness leaflet and the risk output from the CanRisk tool. The breast awareness leaflet is in line with current NICE guidance covering all the required fields (i.e., 5-point NHS plan for being breast aware, when to examine your breasts, what to look for, changes to look for, lifestyle advice, and further information). A copy of both the letter and risk output is also sent to the participants’ GP. Women with an estimated risk at near population level but with additional risk factors within their family history and those at moderate or high risk receive a results letter informing them that they may be at above average population level risk for breast cancer and advise them to make an appointment to discuss with their GP. They are also sent the breast awareness leaflet, and a copy of both the letter and risk output is sent to the participants’ GP. The GP or a delegate practice staff member adds the appropriate codes to the medical records for all participants.

**Table 1 pone.0336902.t001:** Risk categorisation.

Risk	Near population risk	Moderate risk	High risk
Lifetime risk between ages 20 and 80	<17%	≥17% - < 30%	≥30%
Risk between ages 40 and 50	<3%	≥3% - < 8%	≥8%

Women confirmed to have additional risk factors based on their family history or those at estimated moderate or high risk for breast cancer are offered referral to the regional clinical genetics service using a specially designed referral proforma. Women referred to the regional clinical genetics service are then managed in line with current practice.

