### Sample size

Based on an uptake of 16% in the only study in the UK that invited women to complete a breast cancer risk assessment [35], we estimate that to recruit 1,000 women we need to invite approximately 5,000 women from across the GP practices.

Based on distributions of known risk factors in the UK, we estimate that approximately 17% (170) of those 1,000 women will be at above population-level risk [1]. This will allow us to estimate:

the proportion of eligible women in each practice who consent to take part in the study with an accuracy of +/- 1.1% (width of the 95% CI) based on an estimate of 20%the proportion of eligible women in each practice who consent who complete the risk assessment with an accuracy of +/- 2.5% based on an estimate of 80%the proportion of women who consent who are at moderate or high risk on initial CanRisk assessment in general practice with an accuracy of +/- 2.5% based on an estimate of 17%the proportion of those at moderate or high risk who attend for an appointment with a GP and who are referred to secondary/tertiary care with an accuracy of +/- 5.7% based on an estimate of 80%

Allowing for a 40% loss to follow-up, 1,000 participants will allow us to detect a change in anxiety or worry of 0.5 SD or greater at each time point at p < 0.05 and 90% power in both women at population level risk and in the subgroup identified at moderate or high risk. 1,000 participants will also allow us to detect an estimated increase in the proportion of registered women identified at moderate and high risk through proactive multifactorial risk assessment across all the participating practices compared with the 12 months prior to the study with a 95% confidence interval of +/- 0.005 (5 per 1,000 registered women).

Together with data on the acceptability of the proactive multifactorial breast cancer risk assessment, the following progression criteria will be evaluated to judge whether a subsequent full trial of proactive multifactorial breast cancer risk assessment would be feasible: 16% uptake into the study; 60% response to follow-up questionnaires; 80% of women receiving their breast cancer risk and offered subsequent risk management advice/referral. If any of those criteria are not met, we will use the data from the process evaluation to adapt the approach for subsequent feasibility and/or pilot studies before consider progressing to a subsequent full trial.

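### Comparator practices are not required to refer to the one genetics clinic that supplies their numerator, so routine identification may be undercounted by an unknown amount

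*Protocol article*

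**What the plan says.** All of this is in the Protocol article.

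- **Practice recruitment.** The practices approached were those "that refer patients at increased risk of developing breast cancer to the clinical genetics service at the Cambridge University Hospital NHS Foundation Trust".
- **Study outcomes and measures.** The proportion of registered women found to be at moderate or high risk is compared with women so classified "after referral to secondary/tertiary care at non-participating practices across Cambridgeshire and Peterborough during the same time period". It is "also compared with the proportion of registered women aged 40–48 years at participating practices in the 12 months prior to the study".
- **Data collection, numerators.** The extraction covers referrals and "the outcomes of those referrals for all practices across Cambridgeshire and Peterborough for the period of the study". These data "will also be extracted from the electronic health records at the clinical genetics clinic at Cambridge University Hospitals NHS Foundation Trust". No other source is named for non-participating practices.
- **Data collection, denominators.** "Data on the number of women registered at each practice will be extracted from publicly available National General Practice profiles".
- **Risk categorisation and returning risk assessment results.** Women flagged by the study "are offered referral to the regional clinical genetics service using a specially designed referral proforma".
- **Sample size.** Precision for the increase in women identified is given only as "compared with the 12 months prior to the study with a 95% confidence interval of +/- 0.005 (5 per 1,000 registered women".

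**The concern.** Participating practices were chosen on a feature that makes their cases visible in the numerator source: they refer to the Cambridge clinic. The study's own proforma then sends flagged women to the regional genetics service. Comparator practices are not chosen on that feature. One that refers elsewhere would add all its registered women to the denominator and few or no cases to the numerator, even if its routine care is finding such women.

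There is a second, smaller mismatch. The outcome is worded for secondary or tertiary care, but the source is a single genetics clinic. A woman assessed in some other secondary-care service would be missed even if her practice also refers to Cambridge.

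Missing comparator cases can only lower the routine-care proportion, so any such loss favours the intervention. The comparison affected is part of the answer to the third specific objective, on whether proactive assessment identifies more women than routine care.

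**Working it through.** **1. The nearest stated figure.** The plan gives no precision for the concurrent comparison. It gives ±0.005 for the comparison with the prior 12 months.

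Inputs from the Sample size section: about 5,000 women invited, and 17% of 1,000 = 170 above population-level risk. Assumption: 5,000 stands in for the number of registered women.

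- As a single proportion: p = 170/5,000 = 3.4%; 1.96 × √(0.034 × 0.966/5,000) = 0.0050.
- As a difference, 1.96 × √[p(1−p)/5,000 + r(1−r)/5,000], with an assumed prior-year rate r of 0.1% to 1%: 0.0051 to 0.0057.
- With the plan's 80% who attend and are referred, 170 × 0.8 = 136 and 136/5,000 = 2.72%; the same difference formula gives 0.0046 to 0.0053.

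The stated ±0.005 is reproduced at its one-digit rounding. It belongs to the before-after comparison.

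**2. Coverage side by side.**

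| | Participating, study period | Participating, prior 12 months | Non-participating, study period |
|---|---|---|---|
| Practices chosen as referring to Cambridge | Yes | Yes (same practices) | Not required |
| Numerator source | Cambridge clinic | Cambridge clinic | Cambridge clinic |
| Denominator | Registered women | Registered women | Registered women |

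Only the last column lacks a rule tying the denominator to practices whose cases can reach the numerator.

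**3. Size of any bias.** Let r be the true routine-care proportion in the comparator and f the share of those cases that pass through the Cambridge clinic. Neither is in the document. Cases in participating practices are taken as fully captured.

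- Observed routine proportion = f × r.
- Overstatement of the difference = r − f × r = r(1 − f), which cannot exceed r.
- Inflation of a ratio = 1/f.

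If a share q of comparator women belong to practices that refer elsewhere, with the same routine rate and none of their cases recorded at Cambridge, then f = 1 − q.

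Overstatement of the difference, in percentage points:

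| Assumed r | 10% missed | 20% missed | 30% missed | 50% missed |
|---|---|---|---|---|
| 0.1% | 0.01 | 0.02 | 0.03 | 0.05 |
| 0.5% | 0.05 | 0.10 | 0.15 | 0.25 |
| 1.0% | 0.10 | 0.20 | 0.30 | 0.50 |
| Ratio inflated by | 1.11 | 1.25 | 1.43 | 2.00 |

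**4. Illustration.** Take 2.72% in participating practices (136/5,000, assuming the clinic confirms all who are referred) and r = 0.5%.

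- f = 1: difference 2.72 − 0.50 = 2.22 points; ratio 2.72/0.50 = 5.4.
- f = 0.8: difference 2.72 − 0.40 = 2.32 points; ratio 2.72/0.40 = 6.8.
- f = 0.5: difference 2.72 − 0.25 = 2.47 points; ratio 2.72/0.25 = 10.9.

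**The case against.** The strongest reply is that no loss has been shown. Nowhere does the article say that a practice in the area refers elsewhere. It calls the service regional, and the extraction is described as covering all practices, which presumes that the clinic receives their referrals. The clause under Practice recruitment may simply describe the usual local route and not pick out a subset. This stands. A reader might infer from the selection clause that routine identification *is* undercounted, but the document supports only that it may be, by an amount it gives no means of estimating.

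The second reply is that the effect is small and little hangs on it. The Analysis section promises confidence intervals for proportions and differences in proportions; no ratio is planned. On the difference scale the illustration moves by 0.1 points at 20% missed, against a difference of 2.22 points. The third objective also uses the before-after comparison and expected numbers from population-based studies, and no progression criterion uses the concurrent comparison. This also stands. A reader might infer that the objective as a whole is compromised; it is not. The before-after comparison uses the same Cambridge-referring practices throughout, so the practice-selection mismatch does not arise there, although the wording mismatch on secondary or tertiary care could still touch it.

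The third reply is that catchment detail belongs in a fuller protocol or analysis plan. This stands only in part. A fuller document may settle the catchment, but the selection criterion, the comparator and the data source are all stated in the article and, as stated, do not cover the same practices.

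The last reply is that a filter built from referrals seen at the clinic would drop practices that truly made none and so inflate the routine rate. That is right, and the fix must avoid it.

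**Conclusion.** The concern holds as a possible, one-directional undercount in the concurrent comparison. Comparator practices are not held to the referral criterion used for participating practices, and the outcome wording is broader than its single source. If every practice in the area uses the Cambridge clinic and no routine assessment takes place elsewhere, the bias is zero. Otherwise it is r(1 − f): from 0.01 to 0.50 percentage points over assumed routine rates of 0.1% to 1% and missed shares of 10% to 50%. Relative to the routine rate it is larger, and a ratio drawn from the results would be inflated by 1.11 to 2.00 over the same missed shares. All of these values of r and f are assumptions. The point does not overturn the third objective, but it is worth correcting because the direction is known and the correction is cheap.

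**What to change.** - Restrict comparator practices to those whose designated referral route for at-risk women is the Cambridge clinical genetics service. Apply this to numerator and denominator alike.
- Define the criterion from the referral route or catchment and not from referrals observed during the study, so that practices with truly zero referrals stay in.
- Keep the comparison with all non-participating practices as a sensitivity analysis.
- Define the outcome, in all groups and periods, as moderate or high risk identified through the Cambridge clinical genetics service.
- If the clinic is the designated route for every practice in the area, say so in one sentence; the restriction then changes nothing and only the outcome wording needs aligning.

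The cost is a somewhat smaller comparator and a narrower outcome, plus the work of establishing each practice's designated route. The article does not say that such a list exists for the whole area. The extraction is described in the future tense, so the change appears still possible.
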